## Interventions

### Explanation for the choice of comparators {6b}

For this study, a randomized controlled trial will be used to compare a modified version of the Flinders Program with usual care for adolescents with a chronic illness. The aim of the intervention is that it will lead to improved therapy adherence beyond that expected in the context of usual care. Study participants will be randomly allocated to one of the following study arms (Fig. 1). The control group will receive standard care which consists of usual patient care practices which are offered by the patient’s individual specialist treating team. In practice, this will be general advice on self-management behaviors to a variable degree and frequency. Participants in the control group will be provided with a general information brochure after randomization providing encouragement for participants to think about the concept and goals of self-management. Initial control participants will be advised that they will be contacted to start the program in 6 months’ time.

Disease-specific measures can identify the differential effects of specific aspects of a disease or its treatment allowing for comparisons [6]. The controls must be on a specified medication and/or treatment for their chronic disease to allow for comparison using both objective (specific markers of illness control) and subjective measures (participant questionnaires). We believe this approach is the most robust measure of optimal control and is the most satisfactory marker available. Specific targeted interventions to promote self-efficacy and develop self-management skills in adolescents with a chronic illness who are transitioning to adult services are not currently routinely delivered in pediatric settings. There are no other self-management programs that are delivered within our institution and the management of therapy adherence is addressed in an ad hoc manner by individual clinicians. This study will also address the lack of evidence available on the effectiveness of self-management programs specifically designed for adolescents with a chronic condition.

### Intervention description {11a}

The Flinders Chronic Condition Self-Management program, commonly referred to as the Flinders Program™ is a validated, internationally recognized program that is designed for adults, and developed from the South Australia HealthPlus Coordinated Care Trials [44] at Flinders University, Adelaide, Australia. It is a structured, generic, individualized program that incorporates the use of specific standardized tools based on the Theory of Planned Behavior (TPB) [45] and utilizing cognitive behavior therapy techniques and motivational interviewing to assess self-management behaviors. The TPB is centered on the assumption that individual’s make logical, reasoned decisions to engage in specific behaviors by evaluating the information which is available to them and that altering specific beliefs can result in positive behavioral changes [45]. The Flinders Program™ involves the application of three key specific assessment tools: the Partners in Health (PIH) Scale, Cue and Response (C&R) Interview, and the Problems & Goals (P&G) Assessment which are founded on the principles of self-management. These assessment tools provide a formal, systematic approach to assessing self-management skills and problems, and support goal setting that leads to the development of a self-management care plan. The care plan incorporates mutually agreed issues and goals which the participant has agreed to work towards over 6–12 months, with monitoring and reviews at 3, 6, and 12 months either via telehealth, in person or phone on a day and time agreed between the young person and health professional [46].

The structured program incorporates the principles of person-centered care which includes a collaborative, consistent, and reproducible approach to the assessment of self-management behaviors, problem solving, goal setting, and individual care planning [46, 47]. This model of self-management has been evaluated and used clinically in a variety of settings, across a range of chronic conditions. Although the Flinders Program™ is generally used in older adult populations, there is some evidence of its use in adolescents with a chronic illness such as cystic fibrosis, asthma, and diabetes [48]. Our approach is unique in that the program is delivered only to the adolescent and does not include standard parental involvement.

The study will be carried out in collaboration with the Flinders Human Behavior and Health Research Unit (FHBHRU) at Flinders University, Adelaide, Australia, in order to inform the development of an adolescent version of the successful and validated Flinders Program™. A modified version of the Flinders Program™ is already being used in the nurse-led self-management support (SMS) clinic in the Department of Adolescent Medicine at The Children’s Hospital at Westmead, Sydney, Australia. The modifications to the Flinders Program™ were piloted in this clinic with collaboration and agreement from the Flinders team. Modifications made to the program were based on our clinical experience and feedback received from the young people. The main modifications included a preference for individual rather than group sessions, a need for flexible goals which are reviewed more frequently than in adults and some minor changes made to the language used in the original Flinders Program™.

The delivery of the intervention is to the individual rather than as a group. A group format may have advantages from the peer support viewpoint, but the researchers have also identified from unpublished pilot work that adolescents will only attend long term if self-management is part of routine health care visits. Contamination at site will be avoided by the multiple specialist clinics in which this intervention is offered. Therefore, it is unlikely that participants in either the intervention or control group will come into contact with each other. The initial session of the structured modified version of the Flinders Program™ is delivered face-to-face in a clinical environment and takes approximately 90 min to complete, in total, with a shorter time frame of 60 min for follow-up sessions which can be delivered via telehealth. This is an important consideration given the current and continuing COVID-19 situation in Australia. We know also from our clinical experience that the initial face-to-face visit appears to improve engagement and trust in the process.

Following randomization, participants in the intervention group will receive a 12-month nurse-led modified version of the Flinders Program™ plus standard care, while participants in the waitlist control group will receive standard care for 6 months before crossing over to the intervention group until all participants are exposed to the program as demonstrated in the study design diagram in Fig. 1. Participants in the intervention group will receive the Flinders Program™ which will be delivered individually, using a combination of face-to-face and telehealth sessions by members of the research team who have been trained in the delivery of the Flinders Program™. The initial face-to-face session will be undertaken in a private room within a clinic environment. Subsequent follow-up sessions will be offered via telehealth modality, either a video conferencing platform or telephone depending on the young person’s preference. Between the delivery of the initial session and 3 months follow-up, participants will receive follow-up consisting of a maximum of 3 phone calls (every 3 weeks), on a date a time agreed between the nurse and the patient. Participants will receive a booster session at 6 months to maintain engagement, monitor progress, and provide feedback and motivation to help them achieve their self-management goals. There is a final follow-up session at 12 months. Figure 1 outlines this process.

#### Initial assessment of self-management

All participants complete the PIH Scale, a self-rated questionnaire, based on their individual perception of their self-management capabilities. The participant rates their answers on a 9-point scale ranging from never (0) to always (8). This is followed by the C&R interview which is administered by a health professional and uses open-ended cue questions to explore in more detail the patients’ responses to the same 12 questions in the PIH scale. This enables the identification of the participant’s understanding and knowledge, as well as the barriers and enablers to self-management. The C&R interview is scored using the same 9-point scale as the PIH scale by a member of the research team trained in the Flinders Program, and the scores are compared and discussed with the participant. Scores of 4 or below (out of a total maximum score of 12) and discrepancies of 3 or more on either side of 4 rated by the participant or the health professional are flagged as issues requiring further discussion and are addressed in the care plan [46]. The health professional uses open-ended questions to identify the participant’s main problems, impact of chronic illness, and feelings to foster collaboration and partnership. This leads to the development of agreed short- to medium-term goals (3 to 6 months) to address the identified problems. These target issues are then integrated into the negotiated individualized care plan which is reviewed at follow-up [46]. The participant is provided with a copy of the care plan which is either sent to their personal email address or posted in the mail directly to them. A clinic letter is sent to the referring specialist and parents/carers indicating that the adolescent has commenced a self-management program which is directed at increasing autonomy and goal setting and does not contain any details of the intervention.

#### Follow-up data collection

Adherence to prescribed treatment regimenBaseline observations will be collected from both the waitlist control group and the intervention group before randomization. Potential participants in the intervention group will be contacted via phone by a member of the research team. Follow-up of participants in the intervention group will be undertaken by a member of the research team via phone or telehealth (depending on the young person’s preference) at 3, 6, and 12 months to follow-up on adherence to the prescribed treatment post intervention. Participants who do not respond to 3 attempts to contact them at any time point will be treated as missing data.

Information from the participants will be obtained by completing the PIH scale via a semi-structured interview. Subsequently, participants allocated to the wait list control group will be contacted by phone by a member of the research team and provided with a self-management information brochure, with no further contact from the research team. At 6 months, participants in the waitlist control group will be contacted by phone by a member of the research team and invited to participate in the intervention as described for the initial intervention group.(b)Markers of illness control and unplanned hospital visits

The research team will obtain standard measures of illness control for all participants who have been recruited into the study and who have consented to clinical information being obtained for research purposes. The control of chronic illness is the best quantitative measure of therapy adherence that is available. This will be undertaken by way of the research team extracting information from the electronic medical records (EMR) and the young person’s primary physician contacted for further information. Data on unplanned hospital visits will be retrieved by the research team from EMR and/or accessed through the young person’s My Health Record if available.

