### Objectives and hypothesis {7}

#### Primary research question

Does a modified adult chronic condition self-management program plus standard care improve therapy adherence in adolescents aged 15–18 years with a chronic condition compared to standard care only?

The *primary objective of this stud*y is to investigate the effectiveness via adherence of a modified adult chronic condition self-management support program in an adolescent population with a chronic condition within a tertiary pediatric hospital setting, compared to those receiving routine care services in the same setting using standardized markers of improvement in control of their chronic illness.

The *secondary objectives* include the use of routinely collected data on the number of unplanned or unscheduled health care or emergency department visits, together with questionnaire measures of quality of life, self-efficacy, time management, health-related distress, and feasibility and acceptability of the program to further refine its delivery under clinical conditions.

*Study hypothesis* to be tested is that a modified adult-focused, generic chronic condition self-management support program provided to adolescents with a chronic condition who are in the active phase of transition to adult services would:Be more effective than standard usual care in achieving adherence to chronic condition management as measured by quantitative condition-specific validated markers of improvement in illness control as described in Table 1.Be more effective than standard care in improving more global quality of life, self-efficacy, time management, and in reducing health-related distress as described in Table 2.

**Table 1 Tab1:** Markers of illness control

Chronic condition	Measures of illness control	Definition of improvement^*^
Cystic fibrosis	▪ FEV1	FEV1% of predicted increased by ≥ 10%
Type 1 diabetes mellitus	▪ HbA1c	Absolute decrease in HbA1C by ≥ 1% (e.g., 9% reducing to 8%)
Inflammatory bowel disease	▪ Weight	Absolute increase in weight by ≥ 5%
Chronic kidney disease	▪ GFR	Absolute increase in GFR by ≥ 5%
Asthma	▪ FEV1	FEV1 % of predicted increased by ≥ 10%
Epilepsy	▪ Number of seizures	Based on individual and type of seizure as negotiated with treating Neurologist.

Abbreviations measures of illness control: *FEV1 (%)* forced expiratory volume in 1 s, *HbA1c* glycosylated hemoglobin (mmol/mol), *GFR* glomerular filtration rate (mL/min)

Weight (kilograms)

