### Trial design {8}

This is a pragmatic, two-site, two-arm, parallel, longitudinal randomized controlled trial, using both quantitative and qualitative research methods. Participants are allocated at a ratio 1:1 to the intervention or usual care using a computer-generated random list. An RCT design was chosen for this study due to its accepted applicability in assessing the effects of new healthcare interventions such as a self-management program [37, 38]. This study design has been shown to demonstrate sound methodological evidence [39], and allows for a comparison group at each time period and for analysis between each cluster [37, 40]. The study protocol received approval by The Sydney Children’s Hospitals Network Human Research Ethics Committee, Sydney, Australia. The study protocol has been developed based on the Standard Protocol Items: Recommendations for Interventional Trials (SPIRIT) guidelines Schulz and Grimes [41] (see Additional File 1). Figure 2 demonstrates the flowchart of the study design.

This protocol describes an RCT to demonstrate the efficacy of the Flinders Program™ in adolescents. Following randomization, participants in the intervention group will receive a 12-month nurse-led modified version of the Flinders Program™ plus standard care, while participants in the waitlist control group will receive standard care for 6 months before crossing over to the intervention group until all participants are exposed to the program as demonstrated in the study design diagram in Fig. 1. Given that the data available suggests continuing deterioration without intervention is expected, we consider it ethically responsible to offer the intervention to both participant groups.

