### Sample size {14}

The primary outcome of a response to treatment is defined by improvement in disease markers listed in Table 1. We estimate that fewer than 15% of participants would show improvement in disease under usual care, and the intervention would only be considered worthwhile implementing if it can improve responses by a substantial margin. A study conducted by Rhee and colleagues, which evaluated the effectiveness of a self-management program for adolescents with asthma, found overall the intervention group reporting greater improvements in outcome measures; knowledge, self-management skills self-efficacy, and Quality of Life (QOL), than the control group [66]. A study of 54 participants (27 per group) will have 80% power at 5% two-sided alpha to detect a difference in response rates between treatment arms if the rate under usual care is 15% or less and the true difference in proportions is at least 35%, using a chi-square test. To allow for some loss to follow-up, we plan to recruit a total of 60 participants. Participants who withdraw from the study will not be replaced as the power analysis allows for attrition. Participants who withdraw from the study, may have their clinical outcomes determined from their medical records to ensure that the results of the research study can be measured accurately.

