## Assignment of interventions: blinding

### Who will be blinded {17a}

This trial is not blinded. As with all studies of this type of intervention, it is not possible to blind trial participants or the researchers who must know what group the participant is assigned to. To avoid potential bias during the statistical analysis of the trial, the data analyst will be blinded until the entire analysis has been completed.

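### The yes/no primary outcome is extracted by the unblinded team whose members deliver the programme, some criteria are negotiated with no fixed timing relative to allocation, and blinding only the analyst does not protect against this

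*Protocol article*

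**What the plan says.** The primary outcome is a binary call, improved or not, on a condition-specific marker and sustained over 12 months from baseline (Protocol article, Table 1 and its footnote; Measures of illness control).

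- **Who collects it.** Follow-up data collection, part (b), describes the "research team extracting information from the electronic medical records (EMR) and the young person’s primary physician contacted for further information". No trigger or limit is given for contacting the physician.
- **Who delivers the programme.** Under Intervention description, trained members of the research team do.
- **Blinding.** Who will be blinded {17a} says that "it is not possible to blind trial participants or the researchers who must know what group the participant is assigned to". The only blinded role is the data analyst.
- **What specialists learn.** Under Initial assessment of self-management, "A clinic letter is sent to the referring specialist and parents/carers indicating that the adolescent has commenced a self-management program".
- **How improvement is defined.** Table 1 gives numeric thresholds for five of its six conditions. For epilepsy the entry is "Based on individual and type of seizure as negotiated with treating Neurologist". For conditions not listed, Measures of illness control leaves both the marker and the meaning of improvement to consultation with the referring team. It does not say whether this happens before allocation.

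**The concern.** In an open trial, a threshold outcome is protected either by an assessor who does not know the arm or by rules that leave the assessor nothing to decide. The article names no such assessor, and its rules are only partly fixed. A blinded analyst receives a yes or no that is already settled, so analyst blinding cannot correct a reading made with knowledge of the arm.

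The reason given in section 17a applies to people who must know the group, such as those delivering the programme. It gives no reason why the person reading a dated value from a record must know it.

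At stake is the single primary test. With 27 per arm and about 15% responding under usual care, roughly four responders per arm are expected without an effect (27 × 0.15 = 4.05). A few borderline calls in one direction therefore matter.

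**Working it through.** **1. The plan's own figure.** Sample size {14} states: "A study of 54 participants (27 per group) will have 80% power at 5% two-sided alpha", if "the rate under usual care is 15% or less" and "the true difference in proportions is at least 35%, using a chi-square test". Trial design {8} adds "Participants are allocated at a ratio 1:1". With 0.15 against 0.50, the mean proportion is 0.325, and the uncorrected chi-square formula gives

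n = [1.960 × √(2 × 0.325 × 0.675) + 0.8416 × √(0.15 × 0.85 + 0.50 × 0.50)]² / 0.35² = (1.298 + 0.517)² / 0.1225 = 26.9, so 27 per arm.

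Power at 27 is 80.2%, and 54 / 0.90 = 60 matches the recruitment target. The stated size is reproduced and is not in dispute.

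**2. Where discretion remains.**

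| Element | What the article fixes | What it leaves open |
|---|---|---|
| HbA1c, FEV1, weight, GFR | marker, numeric threshold, nominal time points | which recorded value and date count; which visits must meet the threshold for improvement to be sustained |
| Epilepsy | marker (number of seizures) | the criterion, and when it is negotiated |
| Unlisted conditions | consultation with the referring team | marker, criterion, and when they are agreed |
| Physician contact | that it may occur | when it is made, and whether equally in both arms |

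The timing of the criterion cannot be inferred from the timing of baseline collection, because the article gives both orders. Follow-up data collection puts baseline before randomisation; Sequence generation {16a} puts it after. The only stated check of entered data is a 10% double-check by the lead research nurse (Data management {19}).

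**3. Size, as an illustration.** The documents give no misclassification rate, so these are assumptions: no true effect, 15% true response in both arms, 27 per arm, and an expected k intervention participants recorded as improved who are not. The false-positive rate is the sum of Bin(x_C; 27, 0.15) × Bin(x_I; 27, 0.15 + k/27) over all pairs of counts with

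|x_I − x_C|/27 ÷ √[p̄(1 − p̄) × 2/27] > 1.96, where p̄ = (x_I + x_C)/54.

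| Expected k, intervention arm only | Recorded intervention rate | False-positive rate |
|---|---|---|
| 0 | 15.0% | 5.6% |
| 1 | 18.7% | 7.3% |
| 2 | 22.4% | 11.7% |
| 3 | 26.1% | 18.6% |

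If exactly k are upgraded, rather than k on average, the rates are 6.2%, 10.0% and 16.4% for k = 1, 2 and 3.

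**4. The same calculation without one-sidedness.** An equal shift of 0 to 3 in both arms gives 5.6% to 5.7%. An expected two in the intervention arm and one in the control arm gives 7.1%. The inflation comes from the asymmetry, not from misreading as such.

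**The case against.** The other side has a fair case, and parts of it stand.

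- **Objective markers.** HbA1c, FEV1, weight and GFR are numbers in a record, with one preselected marker per condition and set thresholds. This stands and limits the concern for those conditions. It does not reach the negotiated criteria.
- **Who reads what.** A reader might infer that the person coaching a participant also chooses that participant's value. The article says only that the research team extracts and that members of the team deliver. The overlap is possible and not excluded, but it is not stated.
- **What physicians know.** A reader might infer that the physicians who are consulted have been told the arm. The letter goes to the referring specialist, while the further information comes from the primary physician; the article does not say they are the same person. The letter reports that a programme has started, not an arm. Waitlist participants enter the same programme at 6 months, so specialists in both arms may have had such a letter by month 12. Its timing may still reveal the arm.
- **Crossover.** From month 6 the team also delivers to controls, which weakens any presumption of one-sided reading. The documents do not support treating 18.6% as the trial's error rate.
- **Feasibility.** A reader might infer that full blinding is available with present staff. All research staff are programme-trained, no separate extractor is named, and the record can itself show programme contacts. Complete blinding is therefore not shown to be attainable.
- **Detail for the analysis plan.** Visit windows and derived fields are commonly left to it, and the article promises one. Their absence alone would be no finding. The point is the stated route: extraction by the unblinded team, open physician contact and negotiated criteria, with only the analyst blinded.

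**Conclusion.** The concern holds in this limited form and should be acted on, although it does not make the trial uninterpretable. The room for bias is small for the numeric Table 1 markers and larger for epilepsy and unlisted conditions; the documents do not say how many participants these will be.

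The illustrative range of 5.6% to 18.6% rests on 15% response, 27 per arm, no true effect and purely one-sided upgrading of up to three expected participants. None of that misclassification is documented, and symmetric misreading removes the inflation. The sample size is unaffected.

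**What to change.** Amend Follow-up data collection (b), Measures of illness control and Who will be blinded {17a}:

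1. Record each participant's marker and improvement criterion before randomisation, agreed with the treating team where Table 1 gives no number. Reconcile the two statements on whether baseline precedes randomisation.
2. Take the record value closest to the scheduled date within a fixed window. Make any physician query by the same rule in both arms. Let REDCap compute improved yes or no from the entered values and the recorded criterion.
3. Where practicable, have extraction done by an existing team member who does not deliver the programme to that participant, with the allocation field hidden. State that blinding may be incomplete because the record can show programme contacts.

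Steps 1 and 2 help even if blinding is imperfect. The cost is one calculated field in a system already in use, some reassignment of extraction, and coordination between existing staff at the two campuses. Sample size and visits do not change.
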